### Criteria for withdrawal or discontinuation from the study

The objective criteria for discontinuation from study medication and/or institution of another form of treatment include the following:Parent/guardian’s withdrawal of consentDevelopment of a concomitant illness that would interfere with the clear interpretation of study outcomesInability to retain study medication due to vomitingAny serious adverse event requiring treatment withdrawal in the opinion of the study clinician or at the request of a parent/guardianMajor protocol violation, omission of more than one treatment dose, or a credible report of self-medication with an additional anti-schistosomal or antimalarial drug outside the study protocol

### Adverse events

The study nurse administers all the study drugs. Children will ingest the study drugs with a small amount of water. Before administering the study treatment, all the children are given a light meal (slices of bread and a glass of orange juice) to reduce the study drugs’ nauseating effect and improve drug bioavailability [32]. Participants are observed for 1 h after drug ingestion to ensure retention and to assess for any immediate adverse events. Participants who vomit within 1 h of drug ingestion are re-dosed. Participants with repeated vomiting are withdrawn from the study.

All adverse events are elicited by asking the children about any adverse drug reactions observed after taking the study drugs. The symptoms will be assessed, graded (according to their intensity as perceived by the child) by the study clinician, and recorded on the adverse event form. The adverse events form is administered an hour after study treatment and 24 h later (before the next ACT dose). The following information is recorded on the adverse events form: adverse event description, duration (start and end dates); severity grade (mild, moderate, severe); causality (relationship to the study drugs); action(s) taken; and the outcome. The participants who develop adverse events (AEs) or serious adverse events (SAEs) are treated appropriately and followed up until they return to a normal state of health. The investigator reports any SAE occurring or observed during the follow-up period to the KEMRI Scientific and Ethics Review Unit within 48 h of being aware of the event.

### Concomitant treatment

According to the national treatment guidelines, all children with helminthic infections are treated with a single dose of 400 mg of albendazole. A list of prohibited or contra-indicated medicines was availed to the study clinicians. Participants are prohibited from taking any non-study drugs during the study. The study clinician evaluated any reports of non-study medications taken to assess for possible drug interactions.

### Outcomes

The primary efficacy outcomes are as follows:Cure rate at week 6 after starting study treatments, as assessed by microscopy. The cure rate on each PZQ plus ACT arm is compared with that on the PZQ alone arm.The number of participants with drug-related adverse events in the first 24 h after study treatment.

The secondary outcomes are as follows:Cumulative cure rate at week 12 after enrollment, as assessed by microscopy. The cure rate on each PZQ plus ACT arm is compared with that on the PZQ alone arm.Egg reduction rate at weeks 6 and 12 after starting treatment, as assessed by microscopy and intensity reduction rate, comparing each PZQ plus ACT with PZQ alone arm.The prevalence of re-infection at 12 after starting treatment, as assessed as the number of children who were cured at week 6 follow-up but positive for *S. mansoni* at the week 12 follow-up, compared each PZQ plus ACT arms to the PZQ alone arm.

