## Methods

### Study objectives

The overall purpose of the SCHISTOACT study is to evaluate the role of combination therapy in treating schistosomiasis. The primary objective of the study is to evaluate the efficacy (assessed as cure rate by microscopy) and safety (frequency of adverse events) of a single dose of praziquantel combined with a 3-day course of artesunate plus sulfalene/pyrimethamine or artesunate plus amodiaquine or artesunate plus mefloquine or dihydroartemisinin-piperaquine compared with single-dose praziquantel in the treatment of children with confirmed *Schistosoma mansoni* infection.

Our secondary objectives are as follows:To assess the cumulative cure rate at 12 weeks after treatmentTo assess the egg reduction rate at 6 and 12 weeks after treatmentTo assess the re-infection rate at 12 weeks after treatment

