### Randomization and blinding

The randomization (in blocks of 15) list was computer-generated by an independent statistician not involved in participant management. The resulting sequence (randomization number and treatment arm) is stored in opaque sealed envelopes. The enrolling clinician assigns a study number to the participant. The study nurse implements the treatment allocation by opening a sealed envelope for each child according to the assigned randomization number. The laboratory staff are blinded to the treatment allocation, but participants, clinical staff, and data analysts are not.

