The cumulative cure rate at week 12 is assessed by calculating a two-sided difference in proportions of cured children from each PZQ plus ACT arm compared with the PZQ alone arm. Arithmetic mean (AM) egg counts are computed for all non-cured participants. The egg reduction rate is computed as (1 − (AM EPG after treatment/AM EPG before treatment)) × 100. The ERR is expressed as a percentage. Re-infection rate is the proportion of children who test negative for *S. mansoni* at week 6 but test positive at week 12 follow-up. Changes in continuous variables over time are assessed using analysis of variance (ANOVA). The least significant difference will be used to assess post hoc pair-wise comparisons between the group means. Logistic regression will be used for analyses adjusted for the treatment received.

For the primary safety analysis, the frequency and pattern of adverse events are computed by patient counts and percentages in each of the five treatment groups. Adverse events are computed for all participants who received at least one dose of the study drug (intention-to-treat population).

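### The primary safety outcome counts only drug-related adverse events, but the primary safety analysis has no causality restriction; the restricted count is open to arm-dependent attribution in an open-label trial

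*Protocol article*

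**What the plan says.** All references are to the protocol article.

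- **Outcomes.** The second item in the primary list is "The number of participants with drug-related adverse events in the first 24 h after study treatment".
- **Study objectives.** The safety part of the primary objective is given as "safety (frequency of adverse events)", compared with single-dose praziquantel. The abstract likewise names adverse events without mentioning cause.
- **Data management and analysis.** "For the primary safety analysis, the frequency and pattern of adverse events are computed by patient counts and percentages" in each of the five groups, among all children who took at least one dose. No causality condition is attached.
- **Randomization and blinding.** "The laboratory staff are blinded to the treatment allocation, but participants, clinical staff, and data analysts are not".
- **Adverse events.** Symptoms are assessed and graded "by the study clinician, and recorded on the adverse event form". One field on that form is "causality (relationship to the study drugs)". On how events are obtained: "All adverse events are elicited by asking the children about any adverse drug reactions observed after taking the study drugs".

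**The concern.** Two things are at issue. The first is consistency. The outcome is a subset of adverse events selected on judged cause, while the analysis named as primary for safety is not restricted to that subset. A report could present either count as the primary safety result and point to the article in support.

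The second is bias in the restricted count. Whether an event is drug-related is a judgement, and the trial is open-label for everyone except the laboratory. A control child receives one study drug on one day. A child in an ACT arm receives praziquantel plus a multi-drug product over three days, so the same stomach ache has more study drugs to be blamed on. The reverse is also possible: symptoms in an ACT arm might be put down to the infection, or to albendazole, which is given for other helminths and is not a study drug. Safety is compared with praziquantel alone as part of the primary objective, so attribution that differs by arm acts directly on the contrast of interest.

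This point is about which events count. The time window is a separate matter.

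**Working it through.** **Step 1: set the passages side by side.**

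| Place | What is counted | Restricted to drug-related? |
|---|---|---|
| Abstract, Methods | adverse events | no |
| Study objectives | frequency of adverse events | no |
| Outcomes | children with drug-related events | yes |
| Data management and analysis | children with adverse events, by arm | no |

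The abstract and objectives could be read as short labels that Outcomes then specifies. The analysis paragraph cannot be read that way so easily. It states what is computed for the primary safety analysis, and it leaves the restriction out. The firm conflict is between Outcomes and Data management and analysis.

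**Step 2: is the judgement protected from knowledge of the arm?** Children and clinical staff are unblinded. Causality is recorded, but the article does not say who assigns it, gives no attribution rule and describes no blinded review. The study clinician, who assesses and grades symptoms, is the natural candidate, though this is an inference. Any member of the clinical staff would be unblinded.

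**Step 3: what can differential attribution do?** The article gives no adverse event rate, attribution rate, safety margin or safety power, so there is no figure of its own to reproduce. Every input below is an assumption, chosen only to show direction.

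Formula: observed drug-related rate = true event rate × share of events called drug-related.

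*No true difference, 30% of children with an event in both arms:*
- Attribution 60% in control and 80% in ACT: 0.30 × 0.60 = 18% v 0.30 × 0.80 = 24%. Apparent excess: 6 points.
- Attribution 50% in control and 90% in ACT: 0.30 × 0.50 = 15% v 0.30 × 0.90 = 27%. Apparent excess: 12 points.
- Attribution 70% in both: 0.30 × 0.70 = 21% v 21%. No false difference.

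*True difference of 20 points:*
- True 30% in control and 50% in ACT, attribution 90% in control and 60% in ACT: 0.30 × 0.90 = 27% v 0.50 × 0.60 = 30%. The excess shrinks to 3 points.
- True 40% in control and 60% in ACT, same attribution: 0.40 × 0.90 = 36% v 0.60 × 0.60 = 36%. The excess disappears.
- True 30% in control and 50% in ACT, attribution 80% in both: 0.30 × 0.80 = 24% v 0.50 × 0.80 = 40%. Even equal attribution cuts the difference from 20 to 16 points.

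**Step 4: what does an unrestricted count change?** The attribution share drops out of the formula, so the comparison rests on recorded events alone. It does not correct how events came to be recorded. If children are asked about reactions to the drugs, as the Adverse events section describes, some symptoms may never reach the form.

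**The case against.** The strongest reply is that the article already plans the unrestricted table. The only stated primary safety analysis tabulates adverse events by arm with no causality filter, so nothing is hidden and only one word in Outcomes is out of line. Much of this stands. The data for the unrestricted comparison will be shown, and the remedy is mainly one of alignment. It does not remove the point, because the named primary outcome is still the filtered count.

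Other parts of the reply also stand:
- The article does not say who assigns causality. Attribution criteria may be in the full protocol or analysis plan, which are not shown.
- Treatment-related events are a legitimate thing to report, and open-label judgement comes with this design. That supports keeping them as a secondary description. It does not support building the judgement into the primary outcome.
- The safety analysis is described as counts and percentages, with no safety margin or power, so no stated decision rule is threatened. Distorted percentages can still mislead.
- How pre-treatment records are used to separate existing from new symptoms is ordinary analysis-plan detail, and its absence here is no fault.

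A reader might infer that the safety comparison as a whole is decided by attribution, or that unblinded clinicians are known to favour one arm. The documents support neither. The unrestricted tabulation is planned, the assessor is not named, and nothing in the article indicates the direction or size of any attribution difference.

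A reader might also infer that recounting would put everything right because every event is on the form. That sits badly with the elicitation described. The article summarises the procedure and does not show the questionnaire items, and children are also observed for an hour after dosing, so the extent of any loss cannot be judged.

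**Conclusion.** The point holds in a limited form. The primary safety outcome and the primary safety analysis count different events. The outcome as defined passes through a causality judgement that is not described as blinded, in a trial where children and clinical staff know the arm. The drug-related count can therefore create or conceal a difference between praziquantel alone and praziquantel plus an ACT.

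The size is unknown. Under the assumed rates above, the distortion runs from a false excess of 6 to 12 points to the loss of a true 20-point excess. With equal true risks and equal attribution it is zero. These figures show what the definition permits and are no estimate for this trial. The conclusion on inconsistency needs no assumption. The conclusion on bias assumes that causality is assigned by someone who knows the arm, which the blinding statement makes likely but does not establish.

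**What to change.** Amend Outcomes so that the primary safety outcome is the number of children with any recorded adverse event, regardless of judged causality. This brings it into line with Data management and analysis, the objectives and the abstract. Report drug-related events by arm as a secondary description. If causality can still be reviewed without knowledge of the arm, that would strengthen the secondary table, but the main change does not depend on it.

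The cost is a change of wording and a choice of which table is primary. Causality is a separate field on the form, so recorded events can be counted without it. There are two drawbacks. Absolute rates will be higher because they include background symptoms. Child reporting also remains open-label, so it cannot be assumed that background symptoms are reported equally in all arms.

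Trial status gives 30 November 2022 as the end of recruitment, so the first-24-hour data have been collected and the way events were elicited cannot be changed for them. The trial report should state that children were asked about drug reactions and list this as a limitation that re-tabulation does not remove. As the outcome is being changed after data collection in an open-label trial whose analysts are not blinded, the amendment should be dated and both counts reported.

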**Methods:**

The SCHISTOACT study is an open-label, head-to-head, five-arm, proof-of-concept, non-inferiority, individually randomized controlled trial with a follow-up of 12 weeks. A total of 540 primary school-aged children from the Mwea area, Kirinyaga County in central Kenya, diagnosed with *S. mansoni* infection (by Kato-Katz method) are randomly allocated (1:1:1:1:1) to a single dose of praziquantel plus a 3-day course of artesunate-sulfalene/pyrimethamine, or artesunate-amodiaquine, or artesunate plus mefloquine, or dihydroartemisinin-piperaquine, or praziquantel control arm. The primary endpoints are efficacy (cure rate, assessed by microscopy) and safety (adverse events) of each study arm 6 weeks after treatment. Secondary endpoints include cumulative cure rate, egg reduction rate, and re-infection 12 weeks after treatment. The non-inferiority margin is set at − 10 for the risk difference in cure rates between praziquantel and the combined treatment.

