### Study design

The SCHISTOACT study is designed as a phase III, open-label, five-arm, head-to-head, proof-of-concept, individually randomized, controlled, non-inferiority trial. The participants are randomly allocated (ratio 1:1:1:1:1) individually to one of five treatment groups. At baseline, participants in the control arm receive praziquantel (PZQ, single dose of 40 mg/kg). Those in the intervention arms receive a single dose of praziquantel (40 mg/kg) plus a 3-day course of one of four artemisinin-based combination therapies (4 mg/kg of the artemisinin component, once a day for three consecutive days, as fixed-dose WHO-recommended combination treatment for uncomplicated falciparum malaria). The four artemisinin-based combination therapies (ACTs) that are combined with praziquantel are artesunate plus sulfalene/pyrimethamine, artesunate plus amodiaquine, artesunate plus mefloquine, and dihydroartemisinin-piperaquine. These four ACTs were selected because they are widely available for malaria treatment, co-formulated, for once-daily dosing therapy, have a well-established safety profile and have all been evaluated for treating schistosomiasis with inconclusive results. The 6-week interval between the administration of study treatment and evaluation of primary endpoints has been chosen because it corresponds to the duration of schistosome larval maturation. The participants will be followed up at 6 and 12 weeks. During these follow-up visits, stool samples will be collected, and clinical assessments will be performed. All children will receive a standard dose of praziquantel at the end of the study. The study flow chart is shown in Fig. 1.

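### The primary safety outcome is defined in incompatible ways (drug-related events in the first 24 h, or adverse events at 6 weeks), and the 24-h definition does not say which dose starts the clock

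*Protocol article*

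**What the plan says.** The protocol article describes the primary safety outcome in five places, and they do not agree.

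- **Outcomes:** "The number of participants with drug-related adverse events in the first 24 h after study treatment". This stands in the list headed as primary efficacy outcomes.
- **Abstract, Methods:** "The primary endpoints are efficacy (cure rate, assessed by microscopy) and safety (adverse events) of each study arm 6 weeks after treatment".
- **Study design:** "The 6-week interval between the administration of study treatment and evaluation of primary endpoints has been chosen" to match the time that larvae take to mature. Endpoints is in the plural, so safety is included.
- **Study objectives:** "safety (frequency of adverse events", with no window.
- **Data management and analysis:** the primary safety analysis tabulates adverse events by arm for every child given any study drug, again with no window and no restriction to drug-related events.

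Three other parts of the article bear on the 24-h version.

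- **Dosing (Study design; Table 1):** "At baseline, participants in the control arm receive praziquantel (PZQ, single dose of 40 mg/kg", while the four combination arms get praziquantel plus ACT on day 0 and ACT again on days 1 and 2.
- **Adverse events section:** "The adverse events form is administered an hour after study treatment and 24 h later (before the next ACT dose". The form records causality.
- **Randomization and blinding:** "The laboratory staff are blinded to the treatment allocation, but participants, clinical staff, and data analysts are not".

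**The concern.** Safety is a primary endpoint alongside cure, and the question is what the ACT adds to praziquantel. All of the added dosing on days 1 and 2 is in the four combination arms. Whether the headline safety count includes the period after those doses therefore decides what it measures.

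The article offers two windows (24 h and 6 weeks) and two event types (drug-related and all). For the 24-h window it names no starting dose. One reading of that window leaves most ACT doses out of the primary outcome. Another counts more hours in the combination arms than in control. Restricting the count to drug-related events also makes it depend on a judgement by clinicians who know whether the child received one drug or several. Because the analysts are unblinded too, an open definition leaves room to settle it after the arms have been compared.

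**Working it through.** The article gives no event rate, power or sample size for the safety outcome, so there is no stated figure to reproduce. The check compares the texts and works out the hours that count under each reading.

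**Inputs**

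- Control: one dosing day, day 0 (Study design; Table 1).
- ACT arms: three dosing days, days 0, 1 and 2 (Study design; Table 1).
- The 24-h form comes before the next ACT dose (Adverse events section).
- Adverse-event contacts: daily for the first 3 days (Screening, enrollment, and participant follow-up), and in Table 1 at baseline, days 0, 1 and 2, and week 6. Neither place splits the contacts by arm.

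**Step 1: hours that count.** Under a per-dose reading, hours = dosing days × 24. The other windows have one length for all arms.

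| Reading of the window | ACT arms | Control | Ratio | ACT doses with their following 24 h counted |
|---|---|---|---|---|
| 24 h from first dose | 24 h | 24 h | 1.0 | 1 of 3 (dose 1) |
| 24 h after each dose | 3 × 24 = 72 h | 1 × 24 = 24 h | 72/24 = 3.0 | 3 of 3 |
| 24 h from last dose | 24 h | 24 h | 1.0 | 1 of 3 (dose 3) |
| 6 weeks from start | 6 × 7 = 42 days | 42 days | 1.0 | 3 of 3 |

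No 24-h reading both covers all three ACT doses and counts equal time in every arm. The 6-week window does both.

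**Step 2: event type.** The Outcomes section counts drug-related events. The abstract, the objectives and the safety analysis count adverse events without that limit. Changing the window alone would not reconcile these places.

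**Step 3: can a common window be built from the planned contacts?** Largely, yes. The contacts on days 0 to 2 and at week 6 are scheduled for all children. A window from the first dose to 24 h after the last ACT dose would be 72 h in every arm (ratio 1.0) and would cover all three doses. One gap remains: a form 24 h after the day-2 dose falls on day 3, and Table 1 has no day-3 contact.

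**The case against.** The strongest reply is that this is loose wording in a condensed article. Adverse events are scheduled for collection on days 0, 1 and 2 and at week 6, the safety tables carry no 24-h limit, and serious events are reported throughout follow-up. The safety analysis is descriptive: no hypothesis, margin or decision rule hangs on the window. All of that stands, and it limits the severity. It does not remove the conflict, because the article itself states both definitions of a primary endpoint.

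Four stronger readings are tempting but not supported:

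- **That control children are observed for a third of the time.** The scheduled contacts are not split by arm. The 72 h against 24 h contrast concerns the hours counted under a per-dose reading, which the article never adopts.
- **That a false excess of known size follows.** Assuming an independent background risk of 5% per 24 h gives 1 − 0.95³ = 14.3% against 5.0%; at 30% it is 1 − 0.70³ = 65.7% against 30%. These risks are not in the article. The outcome is also limited to drug-related events, so true background events should not count, and a real excess after doses 2 and 3 would be an effect of the regimen. Inflation arises only so far as unblinded clinicians attribute background events to drug.
- **That toxicity after doses 2 and 3 is hidden.** It would be missing from the primary outcome under the first-dose reading, but not from the data or the general tabulation.
- **That everything after the day-2 dose rests on recall at week 6.** The Adverse events section provides an hour of observation and forms at 1 h and 24 h after treatment.

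Unblinded causality assessment is a disclosed consequence of the open-label design. Counting events of any cause reduces reliance on it but does not abolish reporting bias, since the children know their treatment.

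**Conclusion.** The point holds as an inconsistency in definition. The primary safety outcome has two windows, two event types and no stated starting dose, and it is filed under efficacy. Under the first-dose reading, events after two of the three ACT doses fall outside it. Under the per-dose reading, three times as many hours count in the ACT arms as in control. Both results follow from the dosing schedule alone and need no assumed rate. Any effect on the observed percentages cannot be derived from the article.

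It should be fixed before analysis. It ranks below a must-fix because the safety analysis is descriptive and the data for a common window are scheduled in every arm. That last point assumes that the day-1 and day-2 forms were in fact completed for the control arm.

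**What to change.** Before the arms are compared, reconcile the abstract, Study design, Outcomes and the safety analysis to one primary safety outcome under its own heading: the number of children with at least one adverse event in the same calendar window, starting at the first dose, in all five arms and covering all three ACT dosing days. Use the day 0 to day 2 contacts already scheduled for every arm, adding week 6 if the 6-week window is kept. In addition:

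- Report the drug-related count and the first-24-h count as secondary, and note that causality was judged by unblinded staff.
- Report completeness of the day-1 and day-2 forms by arm. Recruitment closed on 30 November 2022, so missing control-arm forms cannot now be collected.
- Reconcile the Adverse events section, which implies a day-3 form after the last ACT dose, with Table 1, which has no such contact.

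The cost is wording and table shells. There are three downsides. More unrelated events will be counted. Children were asked about adverse drug reactions, so capture of events of any cause may be incomplete. The change must be documented as made after recruitment closed, with unblinded analysts.
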